#### Secondary outcomes

For all secondary outcomes, we will consider the variation between the inclusion (baseline value) and post-treatment value (6 months).

##### Capacity measure: Quality of Upper Extremity Skill Test

Quality of Upper Extremity Skill Test (QUEST) is used to assess upper limb quality of movement [35]. This validated instrument is a criterion-referenced measure. It contains 33 items divided into 4 domains: dissociated movement, grasp, weight-bearing, and protective extension. Some items are detailed into sub-items. Both upper extremities are assessed following a dichotomous scale (2 = able to complete item, 1 = not able to complete item). Administration and scoring last 30 to 45 min. Items scores are summed, and formulas are used to obtain percentages for each domain. Domains percentages are summed and divided by number of domains to obtain a total score which is expressed in percentage. A greater score indicates better capacity of the upper limb.

The QUEST is widely used, both in clinical practice and as a standardized outcome measure in studies evaluating treatments’ efficacy. It is an interesting instrument because it measures a combination of impairments and function. It is used to assess the quality of upper limb movement, but it also measures components of hand function and provides information about movement and postural responses. Parametric studies report an adequate to high inter- and intra-rater reliability in 18 months to 12 years old children [36–40].

##### Participation measure: Pediatric Quality of Life Inventory 3.0 Cerebral Palsy module

To describe children’s quality of life, parents are asked to answer the Pediatric Quality of Life Inventory 3.0 Cerebral Palsy module (PedsQL™ 3.0 CP Module, Parents Report) [41]. It is a brief, simple and valid questionnaire, intended to measure health-related quality of life in a population of children and adolescents with cerebral palsy. It assesses the child’s quality of life among 7 domains: daily activities, school activities, movement and balance, pain and hurt, fatigue, eating activities, and speech and communication. The completion time is 5 min. It is administrated following PedsQL™ Administration Guidelines. The French version used in this trial has been translated by MAPI™ Research Institute.

##### Body structures and functions measure: neuro-orthopedic examination

Neuro-orthopedic examination is detailed and scored in a standardized way. The examination focuses on mobilities of the impaired arm: flexion and abduction of the shoulder, flexion and extension of the elbow, pronation and supination of the forearm, flexion and extension of the wrist, flexion and extension of the fingers, and abduction of the thumb. Examiner assesses the passive range of motion at high and low speed and gives a score of Modified Ashworth Scale (MAS) for each mobility cited. Active range of motion is recorded for the same mobilities.

The results obtained after this examination are scored so that changes can be analyzed. At the first examination, each mobility is scored on a binary scale (0 = normal range of motion, 2 = presence of anomaly). The results of the second examination, 6 months later, are scored in comparison with the first examination, on a 0 to 3 scale (0 = normal range of motion, 1 = lower anomaly, 2 = stable anomaly, 3 higher anomaly).

On the sensory level, examination details the type of trouble (epicritic, thermoalgesic, and/or proprioceptive defect) during a comparative examination. Both sides impairments are recorded. Examiner reports the absence or presence of a deficit.

##### Body structures and functions measure: somatosensory evoked potentials

Based on our hypothesis that motor improvement in impaired limb may be subtended by changes in somatosensory function, we wanted to assess the somatosensory system with an objective measure. Somatosensory evoked potentials (SEP) seem complementary to the clinical examination of sensory perception for two main reasons. In children with UCP under the age of 10, changes in sensory function are difficult to measure consistently using behavioral responses to stimuli [42]. Evoked related potentials responses could detect treatment-induced changes prior to their consistent appearance in behavioral measures, particularly in young children populations [8].

SEP are elicited by electrical stimulation of the median nerve at the wrist, using a 5 channels Synergy Medelec system (Oxford Instruments Medical®). The median nerve is stimulated percutaneously at the anterior face of the wrist (cathode is proximal, anode is distal). Intensity stimulation is minimal intensity causing painless muscular contraction in thenar muscles (usually around 8 mA). Each stimulation block consists of 150 stimuli (frequency is 1 Hz; single stimulus duration is 0.1 ms). The stimulation block can be repeated up to 5 times to obtain the best valid record.

The child is lying down on an examination table in a semi-darkened quiet room. He is encouraged to relax using music, comforter, or parental presence if needed. The recording is performed if the child is sufficiently relaxed. If not, it is delayed, and other attempts are made later on.

The recording electrodes are placed over the following locations, at various levels of the nervous system. One is placed at Erb’s point (ipsilateral to the stimulus) to record N9 potential. One is placed over the sixth cervical spine process to record N13 potential. One is placed on the scalp at C3 (left hemisphere) or C4 (right hemisphere), following the ten-twenty electrode system, to record P14, N20, P27, P45, and N30 potentials. The reference electrode is A1 or A2 on the contralateral ear. Ground electrode is placed on the stimulated arm, on a proximal position as compared to stimulation electrodes.

The analysis period is 50 ms at Erb’s point and cervical point, 100 ms at scalp points. SEP are amplified with a band pass fiber at 3–1000 Hz. Electrode impedance is kept under 10 kOhm. Latency of N9, N13, P14, N20, P27, P45, and N30 of each side are recorded for the study. Calculated measures are N13–N20 interval representing the conduction from dorsal horn of the spinal cord to cortex and P14–N20 interval representing the conduction from sub-cortical level to cortex (brain conduction time). Ratios of delay conduction are calculated as follows: delay of the affected side divided by delay of the unaffected side. Amplitudes of N20–P27 are also calculated to allow the calculation of the amplitude ratio (amplitude of affected side divided by amplitude of unaffected side).

##### Safety outcome

Safety outcome will be evaluated during the 6 months wearing period of PGT Lycra^®^ sleeve upper arm. Safety outcomes will include the number and intensity of adverse events of interest (AEIs). AEIs will be defined as adverse event imputable to compressive therapy and Lycra^®^ wearing, localized at the arm. AEIs will be classified into two subgroups: (i) cutaneous events linked to Lycra^®^ wearing and (ii) compression events linked to compressive therapy. According to the device classification panel from FDA regulation, the PROPENSIX PGT Lycra^®^ sleeve is a class I medical device. In this context and according to French regulations, it will not be mandatory to address a Medical Device Reporting process and a Data Safety Monitoring Board report to conduct this study. To perform this safety assessment, parents will be asked to daily report AEIs and other problems occurring during the Lycra^®^ sleeve pressure garment during wearing period on a parental self-report diary logbook. The diary logbook will be carefully checked by the investigator before the physical examination at each hospital visit (i.e., 3 months and 6 months) using a structured interview. AEIs will be classified at posteriori by the investigator using Bégaud et al. classification (minor/moderate/serious) usually used for drug clinical trial report [43]. Cutaneous events were defined as itchy contact dermatitis, red skin rash, and spots; compression events will be defined as mechanical swelling, arm pain, “Blue hand,” tingling, discomfort, sore thumb, and tightness complaint from a child. The frequency of AEIs will be computed as a percentage of occurred days of AEIs from the total wearing time.

Systolic blood pressure (SBP) and diastolic blood pressure (DBP) will also be measured as a safety outcome using an oscillometer device with a pediatric bladder.

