### Ethical considerations and trial registration

This clinical trial is approved by the Ethics Committee of Lille (Comité de Protection des Personnes Nord-Ouest IV, Lille University Hospital, N° CPP 12/05) and the French competent authorities (ANSM, N° 2011-A01129-32). It is registered at ClinicalTrials.gov under identifier NCT02086214 [25].

According to the Declaration of Helsinki, written informed consent is obtained from both parents of the child before enrollment. On the consent form, participants will be asked if they agree to use their data should they choose to withdraw from the trial. Participants will also be asked for permission for the research team to share relevant data with people from the Universities taking part in the research or from regulatory authorities, where relevant. This trial does not involve collecting biological specimens for storage. The consent form and information material are written in French and are available on request, from the corresponding author.

This protocol follows French regulations regarding biomedical research on medical devices. The trial sponsor did not judge necessary to establish a Data Safety Monitoring Board regarding the absence of specific risk. Serious adverse reactions are collected during the whole course of the trial and systematically reported to the principal investigator and safety department of the clinical trial sponsor. Any modification to this protocol is agreed by the ethics committee before implementation and notified to the health authorities in accordance with local rules.

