**Fig. 2 Fig2:**
[figure not shown]
Experimental design. AHA, Assisting Hand Assessment

After giving their consent, participants are recruited and randomized during the inclusion visit (V1) which happens 1 month before the beginning of the intervention. The occupational therapist or investigator, specifically formed, takes precise measurements of the child’s arm, following the manufacturer’s instructions. The investigator sends the measurement data to Medical Z®, so that the confection of the sleeve can begin by the manufacturer according to randomization list (active sleeve or placebo sleeve), on condition of anonymity. The sleeve will be delivered by the manufacturer to the study center within 15 + 3 days. The investigator delivers the tailor-made sleeve (active or placebo) to the child and parents during the baseline visit (V2), with oral and written instructions regarding its utilization and care. In addition, the investigator edits the recommendations for rehabilitation harmonization, destinated to therapists involved in the child’s usual care. The sleeve is reclaimed at the end of the study. Involved therapists, investigators, patients, and their parents are blinded regarding the type of sleeve (active or placebo) received by the child according to randomization.

Outcomes evaluation occurs 1 month after inclusion, during the baseline visit (V2), and at the end of the intervention, after 6 months of daily wear of the Lycra^®^ sleeve, and during the final visit (V4). Baseline and final testing are realized without wearing the splint. AHA, the primary outcome, is assessed by a certified occupational therapist. QUEST is assessed by the same experienced occupational therapist, following the QUEST manual [35]. Neuro-orthopedic examination is conducted by the investigator following the report form of the study. SEP are recorded by an experienced neurophysiology technician. PedsQL™ 3.0 CP Module questionnaire is completed by the child’s parents. Anthropometric measurements occur at V2, V3, and V4. Compliance is monitored in a diary, specifically developed for the study purpose. Compliance data are checked at V3 and V4. Adverse reactions are recorded as well during V3 and V4.

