### Statistical analysis

The variation of the Assisting Hand Assessment (AHA) from baseline to 6 months is the primary outcome. Secondary outcomes are the Quality of Upper Extremity Skill Test (QUEST), the Pediatric Quality of Life Inventory 3.0 Cerebral Palsy module (PedsQL™ 3.0 CP Module, Parents Report), SEP parameters (N13-N20 interval, P14-N20 interval, ratios of delay conduction, amplitudes of N20-P27 and amplitude ratio), neuro-orthopedic examination (results of the second examination, 6 months later, scored in comparison with the first examination on a 0 to 3 scale: 0 = normal range of motion, 1 = lower anomaly, 2 = stable anomaly, 3 higher anomaly).

Statistical analyses will be independently performed by the Biostatistics Department of Lille University. Data will be analyzed using the SAS software (SAS Institute Inc, Cary, NC, USA), and all statistical tests will be performed with a 2-tailed alpha risk of 0.05. Baseline characteristics will be described for each group, categorical variables will be expressed as frequencies and percentages, and quantitative variables will be expressed as means and standard deviation in case of normal distribution or medians (interquartile range) otherwise normality of distributions will be assessed graphically and by using the Shapiro-Wilk test. No formal statistical comparisons of baseline characteristics will be done; clinical importance of any imbalance will be noted. For the primary analysis, both analyses (ITT and per-protocol) will be considered to support the conclusion of non-inferiority [45]. ITT population includes all randomized participants based on their original group of randomization. Per-protocol population includes all randomized patients excluding those with major protocol violations: patients who do not complete the rehabilitation procedure allocated after randomization, discontinuation for lack of compliance or personal reasons, adverse reaction. For the secondary objectives, we will use only the ITT population.

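### The adverse-event endpoint is restricted to arm events deemed imputable to the sleeve, so the planned safety comparison between groups leaves out off-arm and non-attributed events

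*Protocol article*

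**What the plan says.** The Safety outcome section states that "Safety outcomes will include the number and intensity of adverse events of interest (AEIs"). It then defines these events: "AEIs will be defined as adverse event imputable to compressive therapy" and Lycra wearing, localised at the arm. The two subgroups, cutaneous and compression, are also described as linked to the garment or to the compression, and each has a symptom list. Blood pressure "will also be measured as a safety outcome using an oscillometer device with a pediatric bladder".

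Collection is wider than the endpoint, since "parents will be asked to daily report AEIs and other problems occurring" in a diary logbook. The investigator checks the diary at 3 and 6 months in a structured interview, and "AEIs will be classified at posteriori by the investigator" as minor, moderate or serious. AEI frequency is the percentage of days with an AEI out of total wearing time. The section does not say who decides whether an event is imputable.

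The other event collection uses causal wording too. Under Ethical considerations and trial registration, "Serious adverse reactions are collected during the whole course of the trial". Under Study visits, Table 2 schedules an adverse reactions report at V3 and V4, and the text after Fig. 2 says "Adverse reactions are recorded as well during V3 and V4".

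Trial design gives the comparison of safety outcomes between the groups as a reason for unblinding. The same section says that parents, children, physicians and therapists are blinded for the whole trial.

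**The concern.** In a randomised placebo-controlled trial, causation can be read from the difference between arms without judging any single event. A filter on imputability and site comes before that comparison and removes events from it. A problem the sleeve does cause, but which appears away from the arm or is not recognised as sleeve-related, would not reach the comparison.

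Two consequences need to be kept apart. If attribution is the same in both arms, a real difference between arms shrinks and is harder to detect. If attribution differs between arms, the filter can create or hide a difference. The first follows from the definition whenever sleeve-caused events go unattributed. The second needs a further condition.

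This is a matter of what the article states, not of detail left to an analysis plan: it fixes the adverse-event endpoint by cause and site.

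**Working it through.** The article gives no AEI rate, no attribution rate and no safety test, so there is no figure of its own to reproduce. The calculation below is an illustration. Its inputs from the document are 50 children per arm (Sample size estimates) and two-sided alpha 0.05 (Statistical analysis). The event and attribution rates are assumptions. It compares the proportion of children with at least one counted event, which is simpler than the article's frequency measure.

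**1. Loss of signal when attribution is equal in both arms.** Assume true risks of 50% (active) and 25% (placebo), with a share *a* of events attributed in each arm, independently of cause. The counted risks are p1 = 0.50*a* and p2 = 0.25*a*. With d = p1 − p2 and p̄ their mean:

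- SE0 = √(2p̄(1 − p̄)/50) and SE1 = √((p1(1 − p1) + p2(1 − p2))/50)
- power ≈ Φ((d − 1.96·SE0)/SE1)

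For *a* = 1: d = 0.25, SE0 = 0.0968, SE1 = 0.0935, so Φ(0.644) = 0.74.
For *a* = 0.7: d = 0.175, SE0 = 0.0880, SE1 = 0.0862, so Φ(0.029) = 0.51.
For *a* = 0.5: d = 0.125, SE0 = 0.0781, SE1 = 0.0771, so Φ(−0.363) = 0.36.

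Exact enumeration of the Pearson chi-square test gives nearly the same:

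| Share attributed | Counted risks | Power, approximate | Power, exact |
|---|---|---|---|
| 100% | 50% v 25% | 74% | 75% |
| 70% | 35% v 17.5% | 51% | 52% |
| 50% | 25% v 12.5% | 36% | 37% |

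**2. Behaviour when there is no true difference.** Assume a true risk of 30% in both arms and let attribution vary. Exact rejection rates:

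| Attribution, active v placebo | Counted risks | Rejection rate |
|---|---|---|
| 70% v 70% | 21% v 21% | 5.2% |
| 75% v 70% | 22.5% v 21% | 5.5% |
| 80% v 70% | 24% v 21% | 6.6% |
| 80% v 60% | 24% v 18% | 12% |
| 90% v 60% | 27% v 18% | 19% |

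Equal attribution leaves the test at about its nominal level. Small differences in attribution barely move it, and large ones inflate it clearly.

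**3. Could attribution differ by arm?** The section on Lycra sleeves gives 15 to 25 mmHg for the active sleeve and under 5 mmHg for the placebo. The compression list in Safety outcome includes a child's complaint of tightness. A felt difference in pressure could therefore suggest the allocation to whoever attributes events. Against this, the same section says the sleeves look exactly alike and cannot be told apart. The article contains nothing that settles the matter.

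**The case against.** Several stronger readings are tempting, and the document does not support them.

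- **That safety rests on AEIs alone.** Blood pressure is also a stated safety outcome, is scheduled at V2, V3 and V4, and needs no attribution.
- **That the investigator decides causality case by case.** The text gives the investigator the diary check and the severity grading. It names no judge of imputability. The symptom lists narrow the discretion, and one fair reading is that any listed arm symptom during wear counts. On that reading less is lost among arm events, but off-arm and unlisted problems still fall outside.
- **That attribution replaces randomisation as the basis of the comparison.** Attribution takes place under stated double blinding, and equal attribution does not bias the test when there is no true difference. Unequal attribution is a blinding concern, and parents' reports of tightness or discomfort would share it even in an all-event comparison.
- **That never-exposed children dilute the event rate.** Randomisation is at V1 and the sleeve is handed over at V2. The Statistical analysis section says "For the secondary objectives, we will use only the ITT population", so a reader might infer a diluted denominator. But AEI frequency is divided by total wearing time, to which a child without a sleeve adds nothing. The list of secondary outcomes in Statistical analysis omits safety, as does the list in Table 1, so applying ITT to safety is an inference from heading level.

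Two further points have weight. Pre-listed events are a reasonable focus for a class I garment. And if attribution were accurate, the filter would remove unrelated events and could sharpen the comparison. Both are reasons to keep AEIs as a subset. Neither justifies leaving out the all-event comparison.

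**Conclusion.** The point holds in a limited form. The adverse-event endpoint is filtered by cause and site, the other event collection is worded as reactions, and no comparison of all reported events by arm is described, although a between-group safety comparison is planned and the diary also records other problems. The expected consequence under intact blinding is loss of signal, in the illustration from about 75% power to about 52% at 70% attribution and about 37% at 50%. Those figures rest on assumed risks of 50% v 25%, on attribution that is unrelated to true cause, and on a per-child test that the article does not specify.

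A biased comparison is a possibility and is not shown. It would need attribution to differ materially by arm. The matter is worth correcting because the correction is cheap. It does not touch the primary outcome.

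**What to change.** - Compare all diary-reported and investigator-recorded adverse events by arm, regardless of imputability or site.
- Keep AEIs, split into cutaneous and compression events, as a named subset, reported alongside blood pressure.
- State who judges imputability, and complete any imputability and severity judgements before unblinding.

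The diary already asks parents for other problems as well as AEIs, and Trial design says that coding and data handling run to the end of 2022, so the change needs extra coding and tables but no new collection. Events recorded at visits under the adverse-reaction wording may already have been filtered, so the diary should be the main source. The small downside is that more unrelated childhood events will appear in the tables.

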### Trial design

PROPENSIX is a multicenter, prospective, double-blinded, randomized, placebo-controlled superiority trial using a medical device. The seven French study centers involved are specialized in pediatric rehabilitation. Both parents/children and physicians/therapists are blinded regarding the type of sleeve (active or placebo) used during the whole duration of the trial. Un-blinding will be performed for statistical analysis since it is needed for safety outcome comparison between the groups. Primary aim statistical analysis will be also un-blinded as adherence level is mandatory for future intention-to-treat and per-protocol statistical analysis.

Enrollment into the PROPENSIX study started in December 2012 and has been completed since September 2020. The clinical phase of the study was completed in April 2021. The coding process (neurologic exams, AHA, QUEST, and quality of life tests) and data handling are ongoing until the end of 2022.

Subjects are enrolled by the investigator of each study center. The randomization is centralized. The randomization sequence was provided by an independent statistician (who did not take part in assessing the patients at any point in the study) using computer-generated random numbers structured in blocks. The block size information is not specified in the protocol to ensure that investigators are not able to anticipate treatment arm assignment. The randomization ratio is 1:1. The randomization list is maintained by the sponsor. It has been communicated to the splint manufacturer, Medical Z^®^, ensuring a randomized allocation of the sleeves to each included child, on condition of anonymity.

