### Population

#### Patient’s eligibility

The inclusion criteria are children with ante-natal or peri-natal hemiplegic cerebral palsy, aged 5 to 10, having social insurance, written informed consent. The exclusion criteria are allergy to Lycra^®^, contra-indication to pressure therapy (e.g., skin lesions, allergic contact dermatitis), behavior or speech troubles, treatment with Botulinum Neurotoxin on the involved arm within the preceding 4 months, children under tutorship or curatorship, and predictable lack of compliance.

Patients may be discontinued from this trial at any time, firstly for voluntary discontinuation. Other specific reasons for discontinuing a patient are the administration of Botulinum Neurotoxin on the involved arm during the study and/or compliance under 80%. Any discontinuation is referred as soon as possible to the principal investigator. Data regarding the discontinued patients will be analyzed in the intention-to-treat analysis.

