##### Level of adherence to Lycra^®^ sleeve pressure garment procedure

The level of adherence will be assessed using a conventional paper-based method (Lillo-Navarro C). The diary logbook will collect the daily amount of Lycra® sleeve pressure garment wearing period in number of hours and the reason of non-adherence if the sleeve wearing is under 3 h per day. The level of adherence will be expressed in the percentage of number of days when sleeve wearing reaches at least 3 h per day compared to the length of duration in days (start and end date of wearing period). The frequency of reasons of non-adherence will be computed as a percentage of occurred days of AEIs from the total wearing time.

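### The stated formula for the frequency of reasons for non-adherence counts adverse-event days, so it does not measure what it names

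*Protocol article*

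**What the plan says.** Two sections of the protocol article matter here.

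**Safety outcome.** The section opens with "Safety outcomes will include the number and intensity of adverse events of interest (AEIs". AEIs are split into cutaneous and compression events and graded by the investigator as minor, moderate or serious. The source is a parental diary, in which "parents will be asked to daily report AEIs and other problems". The paragraph on AEIs ends with a day-based measure: "The frequency of AEIs will be computed as a percentage of occurred days of AEIs from the total wearing time".

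**Level of adherence to Lycra sleeve pressure garment procedure.** The diary records the hours worn each day and "the reason of non-adherence if the sleeve wearing is under" 3 h on that day. The level of adherence is the percentage of days with at least 3 h of wear, over the days from the start to the end of the wearing period. The section closes with: "The frequency of reasons of non-adherence will be computed as a percentage of occurred days of AEIs from the total wearing time".

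**The concern.** The closing sentence of the adherence section names one quantity and computes another. Its subject is the reasons why the sleeve was not worn long enough. Its numerator is the number of days with an AEI. Apart from the subject, it matches the AEI sentence under Safety outcome.

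An AEI is only one possible reason for a short day, and a child can have an AEI and still wear the sleeve for 3 h. The computed figure therefore cannot show how often any reason, AEIs included, kept the sleeve off. If the sentence were programmed as it stands, the table of reasons for non-adherence would repeat the AEI-day figure under another title, and the reasons recorded by the parents would go unused.

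**Working it through.** The protocol states no AEI rate and no non-adherence rate, so there is no figure to reproduce. The check applies the stated formula to two constructed children.

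**Inputs**
- Wearing period: 6 months (Daily activities), taken as 183 days. This is an assumption.
- Total wearing time: counted in days of the wearing period. This is also an assumption, since the diary records hours as well.
- Counts of 20 days: assumed, for illustration.
- One reason per short day: assumed.

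**Formulas**
- As written: 100 × (AEI days) / (total wearing time)
- What the name calls for: 100 × (days under 3 h with the given reason) / (days in the wearing period)
- Level of adherence, as the protocol defines it: 100 × (days with at least 3 h) / (days in the wearing period)

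**Child A: 20 days under 3 h, all for a reason other than an AEI, and no AEI**
- As written: 0/183 = 0%
- By reason days: 20/183 = 10.9%
- Level of adherence: (183 − 20)/183 = 163/183 = 89.1%

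**Child B: 20 AEI days, sleeve worn at least 3 h every day**
- As written: 20/183 = 10.9%
- By reason days: 0/183 = 0%
- Level of adherence: 183/183 = 100%

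**Consistency check.** The level of adherence and the frequencies of the reasons for missing it should together account for all days.

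| | Adherence + reasons, as written | Adherence + reasons, by reason days |
|---|---|---|
| Child A | 89.1% + 0% = 89.1% | 89.1% + 10.9% = 100% |
| Child B | 100% + 10.9% = 110.9% | 100% + 0% = 100% |

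As written, child A has 20 short days with no reason accounted for, and child B, who has no short day, is given a non-adherence percentage.

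**Sensitivity to the assumptions.** With 180 days instead of 183, 10.9% becomes 20/180 = 11.1%. If total wearing time were counted in another way, child A would still score 0 and child B would still score above 0. The fault lies in the numerator. The written formula gives the right total only when the number of AEI days happens to equal the number of short days, and even then it gives a single figure that cannot be split by reason.

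**The case against.** **This is an evident copying slip.** The sentence before it says that a reason is recorded for each day under 3 h, so the intended numerator can be guessed and the data exist. That stands, and it is why the point is small. But the formula is stated, not left open, and it is wrong as stated. A detailed analysis plan could copy it forward.

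**Adherence reasons are not a listed endpoint.** The Statistical analysis section does not name them as an outcome. That also stands. The adherence percentage has its own, sound formula, so the discontinuation rule that cites "the administration of Botulinum Neurotoxin on the involved arm during the study and/or compliance under 80"% does not rest on the faulty sentence.

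**A stronger reading of the AEI measure.** A reader might infer that the AEI formula under Safety outcome is also wrong, because AEI days over wearing time mixes how many children are affected with how long events last, and so could reverse the order of the arms. The arithmetic is possible. Take 50 children per arm and 183 days each, so 50 × 183 = 9150 days per arm:
- Active: 15 children with 3 AEI days each, 45/9150 = 0.49%
- Placebo: 5 children with 20 AEI days each, 100/9150 = 1.09%
- Children affected: 30% v 10%

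The documents do not support this as a fault, for four reasons.
- With equal wearing time and these counts, reversal needs placebo events to last on average more than 15/5 = 3 times as long as active ones. The example assumes 20/3 = 6.7 times. The protocol gives no AEI rate or duration.
- The measure is defined in the sentence that names it, and it is a legitimate measure of burden.
- It stands beside the number and intensity of AEIs. Trial design says "Un-blinding will be performed for statistical analysis since it is needed for safety outcome comparison between the groups", but nowhere makes the day percentage the only statistic for that comparison.
- The rule for counting one event, pooled or per-child averaging, and confidence intervals for risk differences are details that a condensed article may leave to the analysis plan.

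What remains is narrower: a day percentage does not show how many children are affected, and the article states no such proportion.

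**Conclusion.** The definition of the frequency of reasons for non-adherence is wrong as written. It counts AEI days, and contains neither a reason nor a day under 3 h. In the two constructed children it gives 0% where 10.9% is right, and 10.9% where 0% is right. The percentages rest on the assumed 20 days and a 183-day period; the conclusion that the formula measures the wrong thing rests on neither.

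The consequence is minor. A descriptive adherence summary is affected. The primary analysis and the level of adherence are not, and the diary data allow a correct figure.

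The AEI day percentage under Safety outcome is valid as a measure of burden. That it would mislead the comparison between arms is not shown by the documents.

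**What to change.** Replace the closing sentence of the adherence section with: *The frequency of each reason of non-adherence is the number of days under 3 h with that reason, as a percentage of the days between start and end of the wearing period.* This uses the same denominator as the level of adherence, so with one reason per short day the two add up to 100%.

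Optional addition under Safety outcome: beside the day percentage, report for each arm the number and percentage of children with at least one AEI, by subgroup (cutaneous, compression) and worst grade.

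The cost is one sentence, best settled before un-blinding for analysis, plus one short table if the optional part is taken up. Hours, reasons, AEIs and grades are already collected under the protocol, so no trial procedure changes. The proportion of children affected ignores how long events last, but the retained day percentage still shows that.
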